## Abstract

**Background:**

There is growing evidence suggesting that prolonged sitting has negative effects on people’s weight, chronic diseases and mortality. Interventions to reduce sedentary time can be an effective strategy to increase daily energy expenditure. The purpose of this study is to evaluate the effectiveness of a six-month primary care intervention to reduce daily of sitting time in overweight and mild obese sedentary patients.

**Method/Design:**

The study is a randomized controlled trial (RCT). Professionals from thirteen primary health care centers (PHC) will randomly invite to participate mild obese or overweight patients of both gender, aged between 25 and 65 years old, who spend 6 hours at least daily sitting. A total of 232 subjects will be randomly allocated to an intervention (IG) and control group (CG) (116 individuals each group). In addition, 50 subjects with fibromyalgia will be included.

Primary outcome is: (1) sitting time using the activPAL device and the Marshall questionnaire. The following parameters will be also assessed: (2) sitting time in work place (Occupational Sitting and Physical Activity Questionnaire), (3) health-related quality of life (EQ-5D), (4) evolution of stage of change (Prochaska and DiClemente's Stages of Change Model), (5) physical inactivity (catalan version of Brief Physical Activity Assessment Tool), (6) number of steps walked (pedometer and activPAL), (7) control based on analysis (triglycerides, total cholesterol, HDL, LDL, glycemia and, glycated haemoglobin in diabetic patients) and (8) blood pressure and anthropometric variables. All parameters will be assessed pre and post intervention and there will be a follow up three, six and twelve months after the intervention. A descriptive analysis of all variables and a multivariate analysis to assess differences among groups will be undertaken. Multivariate analysis will be carried out to assess time changes of dependent variables. All the analysis will be done under the intention to treat principle.

**Discussion:**

If the SEDESTACTIV intervention shows its effectiveness in reducing sitting time, health professionals would have a low-cost intervention tool for sedentary overweight and obese patients management.

**Trial registration:**

A service of the U.S. National Institutes of Health. Developed by the National Library of Medicine. ClinicalTrials.gov NCT01729936

## Background

Obesity is one of the main leading cause of mortality worldwide; in fact according to the World Health Organization (WHO) more than 2.8 million adults die each year because they are obese or overweight. In addition, is one of the main risk factor for many of the leading causes of mortality such as cardiovascular diseases, stroke and certain cancers [1]. The percentage of obese and overweight people worldwide has significantly risen in the past years [2]. Therefore, prevention and reduction of obesity should be a public health priority and mainly include: rising physical activity (PA), lowering sedentary behavior (SB) and modifying the diet to low-calorie and low-fat diets [3].

Sedentary behavior is any waking behavior characterized by an energy expenditure ≤1.5 Metabolic Equivalent Units (METs) while in a sitting or reclining posture [4]. Recently, a range of observational data has reported associations between sedentary time and adverse health outcomes [5], including an increased risk of diabetes, cardiovascular and all-cause mortality [6-8].

Lifestyle changes in high-income countries have led to a decrease in the energy expenditure needed for daily life, an increase in sedentary activities and weight gain. Levels of PA and sedentary behavior among young people tend to promote obesity [9].

The dose–response relationship among amount of PA, energy expenditure and weight loss is obvious [10]. People with overweight and obesity should accomplish 5 sessions of 45–60 minutes of mild-intensity PA per week [11]. Unfortunately, evidence shows the difficulty of overweight and obese population to achieve these recommendations in the long term; PA dropout among them is quite high [12].

In this context, and considering the scarce adherence to PA in people with overweight and obesity, there is recent evidence that interventions to increase energy expenditure perhaps should first focus on reducing time of sedentary activities. It is well known that walking is a simple PA accessible to most people, which can have an important role to increase daily energy expenditure and help reduce SB [13]. Moreover, if obese people could manage to be standing or wandering for 2.5 hours per day instead of sitting, this would represent an extra energy expenditure of 350 kcal per day, and they might find it easier to maintain this activity in the long term [14].

To effectively manage the increasing number of patients with obesity-related chronic illnesses, the medical community should embrace a major role in encouraging patients to make healthy lifestyle choices. Primary care is well suited to fill this need, because most of the population identifies a primary care clinician as their usual source of care [15].

There are few randomized controlled trials that assess the impact of interventions on the reduction in daily sitting time. Additionally, these studies have included small samples. A recent intervention with 92 subjects with type-2 diabetes achieved a reduction in daily sitting time of 23 min/day [16]. Another study with 12 patients with overweight and obesity showed an increase in walking time per day (146 to 203 min/day), increase in number of steps/day (4351 to 7080 steps/day) and decrease in sitting time (1238 to 1150 min/day) [17]. To our knowledge, there is no evidence on the effectiveness of an intervention based on reducing daily sitting time in adults with overweight and mild obesity and its sustainability in the long term.

The aim of the present study is to assess whether a sustained reduction of sedentary time is possible, and if so, to evaluate the effectiveness of an education-based intervention among overweight and mild obese adults attended in Primary Care in terms of reduction of sitting time. Secondary aims are to determine health benefits of the intervention among studied population.

## Method/Design

The present study is a randomized controlled trial (RCT). The intervention evaluated is education-based in order to reduce sedestation time among overweight and mild obese adults attending primary care. The Project SEDESTACTIV includes two phases. Phase 1: a qualitative study already undertaken to know the proposals, barriers and facilitators of overweight or mild obesity users of primary health care (PHC) on reducing sitting time. Phase 2: a randomized controlled intervention trial based on education to reduce sedentary behavior (SB).

### Phase 1. Qualitative data collection and analysis

The qualitative study included focal groups and semi-structured interviews were conducted by an expert moderator and an observer in PHC. 22 overweight or mild obese aged 25–65 years who were 6 or more hours sitting (see study population) participated. Awareness, acceptability and readiness to reduce sedentary behavior (according to importance, motivation and confidence) and opinions about primary care interventions to reduce sitting time were discussed. Facilitators and barriers for change were also asked. The number of subjects was determined by the saturation of the information (n = 22). All participants read and signed the informed consent form. All interviews were recorded, transcribed and analyzed using Atlas.ti, performing a triangulation of analysis. Ethical approval was granted by Clinical Investigation Ethics Committee of the IDIAP Jordi Gol, located in Barcelona.

Qualitative data was used to design the RCT education intervention to reduce sitting time. From these findings we can say that the interventions from PHC to reduce SB in overweight and mild obesity people should include monitoring by a professional and face-to-face follow-up.

### Phase 2. Randomized controlled trial (RCT)

Phase 2 consist of a multi-centric RCT to assess the effectiveness of a six-month primary care intervention to reduce the daily hours of sedestation as well as to increase their weekly caloric spend at the end of the intervention and at short, medium and long term among overweight and mild obese persons. The CONSORT (Consolidated Standards of Reporting Trials) guidelines for RCT were used to design the study and will be used to conduct it [18].

### Study population

Inclusion criteria of participants will include: (a) men and women aged 25–65 seen at the PHC for whatever reason; (b) diagnosed of being overweight or suffer mild obesity (BMI: 25–34.9 kg/m^2^); (c) autonomous subjects who have minimum physical aptitudes to follow the recommendations (being able to walk and stand up from a chair independently); (d) who are ≥6 hours daily sitting; and (e) who can assure its participation in the study for a year.

Exclusion criteria will be based on certain medical conditions which could contraindicate the fulfillment of the intervention. Patients who have had obesity surgery will be also excluded.

Written informed consent will be obtained from all subjects of both intervention (IG) and control group (CG) prior to its inclusion on the study. This trial was approved by the Clinical Investigation Ethics Committee of the IDIAP Jordi Gol and registered at trial NCT01729936.

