### Description of the intervention

#### Intervention group

The intervention will be done according to the patient’s willingness to reduce sitting time (stage of change), and considering whether the subject prefers a more or less intensive intervention: (a) precontemplative (not thinking about change) and contemplative (thinking about change), (b) ready to change with minimum professional support, or (c) ready to change with intensive professional support. All of them will be handed a card with the planned sessions and Mediterranean diet recommendations.

Precontemplative and contemplative patients (a) will be informed of the risks of being 6 or more hours sitting and will be asked about the importance and confidence for change. Ready to change patients (b and c) will be proposed an intervention based on 2–5 meetings (visits face-to-face or phone calls depending on the situation of each professional and patient) with a trained professional during 6 months. On those meetings, the professional will work on finding alternatives to progressively reduce SB by developing the same activities walking.

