### Control group

Subjects assigned to the control group will be given information on the study and will be asked to continue their routine daily activities. They will receive their usual care from their primary care practice. Furthermore, the health professional will give the patient pamphlet with the Mediterranean diet recommendations. They will be followed at the end of intervention and at three, six and twelve months follow-up. At the following visits several parameters will be evaluated (see Outcome measures).

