### Outcome measures

#### Main objective

The primary outcome is sitting time measured by using the activPAL device (PAL technologies, UK). It also will be measured with the Marshall questionnaire [19]. The study measure will be assessed at baseline, at the end of the intervention, and at three, six and twelve months follow-up.

Sitting time will be evaluated, moving from ≥6 hours daily sitting to less sitting time, and increasing the weekly number of METs. The activPAL enables to evaluate caloric expenditure, time sitting/lying, number of steps, standing time, walking time and the transitions from one position to another. This instrument has shown good validity and reliability in general population in a previous study [20]. Marshall questionnaire enables sitting time to be evaluated as a continuous variable by calculating the weekly minutes sitting, and classifying the subjects according to whether they are more or less hours sitting. This instrument has shown good validity and reliability in general population in a previous study [19].

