#### Other specific objectives

Secondary outcomes for IG and CG include: (a) decreasing sitting time in work place in individuals involved in the intervention, measured with Occupational Sitting and Physical Activity Questionnaire (OSPAQ) [21]; (b) description of the development of health-related quality of life measured with EQ-5D (Euroqool Group: http://www.euroqol.org) (first and last session of the intervention, with follow up at three, six and twelve months after the intervention); (c) evaluation the evolution of the attitude towards the change in behaviours in relation to reduce sitting time using the Prochaska scale (Prochaska and DiClemente’s Stages of Change Model) [22]; (d) evaluation of physical inactivity, assessed with catalan version of Brief Physical Activity Assessment Tool (CBPAAT). The CBAFC enables physical inactivity as a categoric outcome and classifies subjects as ‘active enough’ or ‘insufficiently active’. This instrument showed good validity and reliability in general population in a previous study [23]; (e) evaluation of the number of daily steps walked, measured with DigiWalker 200w pedometer and activPAL posture monitor. Reliability and validity of these devices were previously assessed [20,24]; (f) evolution of anthropometric variables: BMI, triceps skinfold and waist circumference; and (g) description of the evolution of triglycerides, total cholesterol, HDL, LDL, glycemia and, glycated haemoglobin in diabetic patients (first and last session and 6 and 12 months after the intervention).

All parameters (not (g) outcome) will be assessed pre and post intervention in both groups and there will be a follow up in a face to face interview three, six and twelve months after the intervention.

Sociodemographic and health data will be also collected (age, marital status, educational level, blood pressure, BMI and associated pathologies).

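### Inclusion criterion (e) asks for one year of participation, but the stated schedule runs to about month 18, so availability for the last assessment is not secured

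*Protocol article*

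**What the plan says.** All of the following is in the protocol article.

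- **Entry requirement.** Under Study population, criterion (e) takes people "who can assure its participation in the study for a year".
- **Length of the intervention.** The Phase 2 section sets out to assess the "effectiveness of a six-month primary care intervention". The Intervention group section describes meetings "with a trained professional during 6 months".
- **Follow-up.** Other specific objectives plans a "follow up in a face to face interview three, six and twelve months after the intervention". The Abstract counts follow-up from the same point.
- **Primary outcome.** Under Main objective, sitting time is assessed at baseline, "at the end of the intervention, and at three, six and twelve months follow-up".
- **Control arm.** The Control group section gives the same visits: "They will be followed at the end of intervention and at three, six and twelve months follow-up".
- **Analysis.** Statistical methods fits multilevel models to the whole path of each person, the 12-month follow-up included.
- **Aim.** The Background section wants to "assess whether a sustained reduction of sedentary time is possible", and the Phase 2 section names short-, medium- and long-term horizons.

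**The concern.** A criterion that asks candidates to vouch for their availability serves to protect retention. It can do so only if the period it names is at least as long as the schedule. Here the period is one year, while the intervention and follow-up together appear to take a year and a half.

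The visit left outside is the final one. It carries the longest-term evidence on whether a reduction in sitting time lasts, and the Background section names long-term sustainability as a gap in the evidence. The visit also enters the planned multilevel models. Staff who apply criterion (e) as written have no ground to decline someone who says at screening that they will be gone after twelve months. That can be corrected before enrolment but not afterwards.

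**Working it through.** No sample-size or power formula bears on this point. It is a sum of durations, followed by a check of whether another reading of the text removes the conflict.

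**Inputs**

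- Participation to be assured at entry: 12 months (Study population, criterion e).
- Start of the clock: baseline, with randomisation after the baseline measures (Recruitment process and randomisation).
- Intervention: 6 months (Phase 2; Intervention group).
- Follow-up: 3, 6 and 12 months, counted from the end of the intervention (Abstract; Other specific objectives).

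**Timeline**

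Month of visit = 6 + months since the end of the intervention.

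| Assessment | Month from baseline | Within 12 months? |
|---|---|---|
| Baseline | 0 | yes |
| End of intervention | 6 | yes |
| 3-month follow-up | 6 + 3 = 9 | yes |
| 6-month follow-up | 6 + 6 = 12 | yes, at the limit |
| 12-month follow-up | 6 + 12 = 18 | no |

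Shortfall: 18 − 12 = 6 months, or 6/18 = one third of the full participation. One of the five assessments, and one of the four after baseline, is not covered. The blood measures have only two follow-ups after the intervention, at 6 and 12 months, so one of those two is not covered.

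**Could follow-up be counted from baseline?** The last visit would then fall at month 12 and the criterion would fit. But the 3-month visit would fall inside the six-month intervention, and the 6-month visit would coincide with the end of the intervention. The Main objective and Control group sections list the end of the intervention separately from, and ahead of, the three follow-ups. The Abstract and Other specific objectives count follow-up from the intervention in so many words. This reading fails.

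**Could the year mean the follow-up year alone?** The criterion speaks of participation in the study, and the intervention is part of the study. If only the follow-up year were meant, the total would still be 6 + 12 = 18 months, and the criterion would need rewording to say so.

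**Could a shorter intervention close the gap?** With the last visit 12 months after the intervention, one year suffices only if the intervention lasts 12 − 12 = 0 months. Any delay between baseline and the first session lengthens the total further.

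**The case against.** The best answer is that one year is a minimum asked at entry. It does not end participation at month 12 or release anyone from later visits, and the last visit is scheduled for both arms. Candidates are also told how the project will run before they sign the consent form, and that information, which is not shown, may already describe the full schedule. All of this stands. It limits the consequence, but it does not make 12 months equal 18.

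A reader might infer more than the text supports:

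- **That participants have committed to miss the last visit.** Nothing in the article says so. The criterion fails to secure attendance at month 18, which is a weaker statement.
- **That the aim of a sustained reduction rests on month 18 alone.** Months 9 and 12 also follow the intervention, bear on whether a reduction lasts, and lie within the year. Only the longest-term assessment is uncovered.
- **That loss will differ by arm.** The intervention meetings end at month 6, a year before the last visit. After that both arms have the same visits. The criterion is applied before randomisation, so it selects equally in both arms.
- **That loss beyond the planned 20% is built in.** The Sample size section does not tie its 20% to any visit, and the article gives no expected attrition at month 18. A higher figure would be an assumption, not a consequence of this wording. The planned models also use all visits, so a complete-case calculation at month 18 would not measure the effect.

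**Conclusion.** The inconsistency is real. The criterion secures one year and the schedule needs about 18 months: six months short, with the last of five assessments uncovered. It changes who may be enrolled, since a person known to be unavailable after month 12 meets criterion (e). The result is a greater risk of missing data at the longest-term visit, of a size that the documents do not allow anyone to state. No estimate, error rate or comparison at the earlier visits is shown to be affected.

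The conclusion assumes that the clock starts at or near baseline, that the intervention takes the stated six months, and that the control arm's visits are timed in the same way. The sum follows directly from the text. How much data would be lost is unknown.

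**What to change.** Reconcile criterion (e) with the stated schedule: require that candidates can assure participation through the visit 12 months after the intervention, about 18 months from baseline. Check that the participant information gives the same duration, and align it if it does not.

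Re-counting follow-up from baseline is not a sound alternative, because it would break the visit schedule as shown above.

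The cost is a wording amendment to one criterion and, if needed, to the participant information. A few candidates may decline the longer commitment, which could slow recruitment slightly. Visits, measurements and analysis stay as they are.

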### Recruitment process and randomisation

Recruitment will take place in 13 PHC in different regions of Spain (Barcelona, Lleida, Zaragoza and Almeria). Primary health care professionals, who were selected on a voluntary basis from each of the participating centers, were trained. During the recruitment period, the opportunity to participate in the study will be offered at least once a week to all patients with overweight or mild obesity. A total of 30 subjects will be recruited in each PHC. Patients who meet the inclusion criteria and agree to participate will be contacted and informed about how the project will be carried out. All of them will be requested to sign the informed consent form to take part in the study. Demographic and health data will be recorded for all participants.Random sequence generation will be computer-generated by an independent researcher, guaranteeing that the allocation groups remain confidential. Participants will be randomized to intervention group (IG) or control group (CG) after baseline measures assessment. Figure 1 shows the flowchart of participants’ recruitment and trial design.

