### Sample size

Since no previous intervention studies on caloric spend had been undertaken –similar studies report sedestation time- we consider that the current intervention is analogous to others proposed in other lifestyles such as tobacco consumption. Accepting an alpha risk of 0.05 and a beta risk < 0.10 in a bilateral contrast, 232 individuals are needed: 116 individuals in the IG and 116 in the CG in order to detect a difference ≥ 0.15 between the two. A proportion of 0.5 in one of the groups is to be assumed. A dropout rate of 20% is estimated. The sample size calculations were performed with the Granmo program (version 7.1).

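### The enrolment figures disagree: 13 centres at 30 each is 390, the trial is sized at 232, and 50 fibromyalgia subjects appear only in the Abstract

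*Protocol article*

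**What the plan says.** Three places in the protocol article bear on how many people enter the trial.

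- **Recruitment process and randomisation.** "Recruitment will take place in 13 PHC in different regions of Spain", and then "A total of 30 subjects will be recruited in each PHC". The next sentences describe contacting eligible and willing patients, consent, baseline measures and randomisation.
- **Sample size.** "Accepting an alpha risk of 0.05 and a beta risk < 0.10 in a bilateral contrast, 232 individuals are needed", split as "116 individuals in the IG and 116 in the CG". The target is a difference of 0.15 with a proportion of 0.5 in one group. A 20% dropout rate is mentioned afterwards, without saying whether 232 already allows for it.
- **Abstract, Method/Design.** The same 232 is given as the number allocated at random, 116 to each group. The following sentence reads "In addition, 50 subjects with fibromyalgia will be included".

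Fibromyalgia is mentioned nowhere else in the text: not under study population, recruitment, intervention, outcomes, sample size or statistical methods.

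**The concern.** A reader who multiplies centres by quota gets a total that matches neither the sample size nor the sample size plus the extra group. The number to be randomised is the figure that links site targets, the power statement and the flow diagram, so it should have one value. As printed, a centre working from the recruitment section and a statistician working from the sample size section would expect trials of very different size.

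The 50 fibromyalgia subjects raise a different problem. The sum does not fail, since the Abstract presents them as additional. But they are an announced group with no stated role. The main comparison is by intention to treat in overweight or mildly obese adults, and the text does not say whether these 50 must meet those criteria, whether they are randomised, or whether they count in that comparison.

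**Working it through.** **Inputs.** Recruitment section: 13 centres, 30 per centre. Sample size section: 232 in total, 116 per group, two-sided alpha 0.05, beta below 0.10, difference 0.15, reference proportion 0.5, dropout 20%. Abstract: 232 randomised, plus 50.

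**1. Totals.**
- Stated total: 116 + 116 = 232, which agrees between Abstract and Sample size.
- Centre quota: 13 × 30 = 390.
- Stated total plus the extra group: 232 + 50 = 282.
- Gaps: 390 − 232 = 158 (158/232 = 68%); 390 − 282 = 108 (108/282 = 38%).
- Quota that each total would need: 232/13 = 17.8; 282/13 = 21.7. Neither is 30.

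**2. Can dropout reconcile them?**
- 232 as completers: 232/0.8 = 290.
- The same with the 50 added: 290 + 50 = 340.
- Inflating the combined figure: 282/0.8 = 352.5, so 353.
- Working back from the quota: 390 × 0.8 = 312, against 232 or 282.

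None of these matches.

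**3. Can screening losses reconcile them?** Only if 232/390 = 59.5% of those counted at the centres went on to be randomised. The text gives no such rate.

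**4. What each total delivers.** This matters because the conflict has to be settled in favour of some number. For two equal groups of n, with p1 = 0.50 and p2 = 0.65 (mean 0.575):

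power = Φ{ [0.15·√n − 1.96·√(2 × 0.575 × 0.425)] / √(0.50 × 0.50 + 0.65 × 0.35) } = Φ{ (0.15·√n − 1.370) / 0.691 }

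| n per arm | Basis | Power |
|---|---|---|
| 116 | 232 randomised, no loss | 64% |
| 92.8 | 232 randomised, 20% lost | 54% |
| 195 | 390 randomised, no loss | 85% |
| 156 | 390 randomised, 20% lost | 77% |

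Taking p2 = 0.35 gives the same values by symmetry. Solving the same formula for 90% power gives n = (1.370 + 1.2816 × 0.691)² / 0.15² ≈ 226.2, so 227 per group (454 in total). With 20% dropout this becomes 227/0.8 ≈ 284 per group (568). The stated 232 is therefore not reproduced from its own inputs. That is a separate defect; it is used here only to show that adopting 232 or 390 does not restore the stated power.

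**The case against.** The strongest defence is that 390 and 232 count people at different stages. The sentence with the quota comes after the description of offering participation and before the sentences on eligibility, consent, baseline and allocation, while the Abstract's 232 is the number randomised. On that reading 30 per centre is a pool from which 232 emerge. The order of the text allows this, and Figure 1, which might settle it, is missing from the text available for this review. What stands is that the sense may be harmless. But the word used is recruited, no screening loss is given, and a centre reading the sentence would reasonably aim to enrol 30. The wording needs correcting on either reading.

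A second defence is that an article may leave details of an add-on group to the full protocol. That is fair for its procedures. It is weaker for the group's existence, because the Abstract announces a group that the body never mentions.

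Three stronger readings are tempting and are not supported:

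- **That recruitment has no end point and could be stopped at will.** The target of 232 is stated twice, and nothing in the text permits a data-driven end. The fault is two competing totals, not the absence of one.
- **That fibromyalgia patients will be pooled and make up 50/282 = 18% of the analysis.** No section says they are randomised or analysed with the others. The eligibility section also excludes unspecified medical conditions that could contraindicate the intervention. Pooling is left open, not planned.
- **That 232 already contains the 20% dropout.** The Sample size section does not say so. The mismatch holds whether it does or not.

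**Conclusion.** The point holds as an inconsistency in the stated number to be enrolled. The centre quota gives 390; the sample size gives 232, or 282 with the extra group; no use of the 20% dropout reconciles them. If the quota were followed to randomisation, the trial would be 68% larger than stated. If the quota means people approached or screened, the trial size is unaffected and the fault is one of labelling, with an unstated randomised fraction of 59.5%.

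The role of the 50 fibromyalgia subjects in relation to the main comparison is not fixed. That is an undefined group, not an arithmetic error.

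The power figures assume 1:1 allocation, 0.50 against 0.65 (or 0.35), a two-sided 0.05 test without continuity correction, and loss of exactly 20% where stated. On those terms neither 232 nor 390 reaches the 90% that the protocol claims.

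**What to change.** 1. State one number to be randomised and give a per-centre quota that matches it: about 18 per centre for 232 (13 × 18 = 234). Alternatively, keep 30 per centre but label it as the number invited or screened.
2. Say whether the total already includes the 20% dropout.
3. Whichever total is kept, restate the power it delivers for 0.50 against 0.65 at two-sided 0.05, with and without dropout. Trimming the quota to fit 232 does not cure the shortfall in power, and nor does adopting 390.
4. State that the 50 fibromyalgia subjects are additional to that total and are not part of the primary intervention-versus-control comparison, whether or not they are randomised, and report them separately. Say in the methods whether they are randomised; the present text does not.

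The cost is wording in the recruitment, sample size and population sections. The downside is that the fibromyalgia group then supports only a separate descriptive analysis, and that the sponsor must state a power below the one now claimed unless the total is raised.
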